## 2. Characteristics of the research population

### 2.1. Overview of the research population

CATCH services are delivered by clinical staff as part of regular care. Our study retrospectively analyzes administrative data for patients with OUD who have been hospitalized at the participating sites. These patients are not recruited or enrolled. The H+H policy is for all patients to sign a general HIPAA release when they first present for care. Patients will not be asked to provide separate informed consent for receiving CATCH services.

We will conduct qualitative interviews to assess implementation outcomes with up to 60 CATCH staff and up to 60 patients (total N=120). A purposeful sampling approach will be used to select participants with a variety of demographic characteristics, and staff selected for interviews will include individuals providing each of the CATCH team roles (i.e., medical providers, addiction counselor/social workers, and peers). Patients will be divided approximately equally between those who did and did not receive CATCH services. Individuals who participate in research interviews will provide informed consent for participation and will be enrolled in the study. Baseline interviews are conducted with CATCH staff (approximately 5/site). Post-implementation interviews are conducted approximately 9-12 months after introduction of CATCH for CATCH staff (approximately 5/site), and approximately 12 – 18 months after introduction of CATCH with patients (approximately 10/site), as summarized in Table 3 below. Distribution of staff interviews at baseline and post-implementation may vary depending on participants' availability and staffing levels at each site, but will be approximately 5 in each case. If an in-person research visit is not feasible (for example, due to travel restrictions related to COVID-19), staff interviews may also be conducted via Webex or phone. In such cases, only audio (and not video) will be recorded and saved.

**Table 3. Number of participants participating in interviews at each study site.\***

| Site: | Bellevue
(N
participants) | Coney Island
(N
participants) | Elmhurst
(N
participants) | Lincoln
(N
participants) | Metropolitan
(N
participants) | Woodhull
(N
participants) | TOTAL |
|-------|---------------------------------|-------------------------------------|---------------------------------|--------------------------------|-------------------------------------|---------------------------------|-------|
|-------|---------------------------------|-------------------------------------|---------------------------------|--------------------------------|-------------------------------------|---------------------------------|-------|

|                                        |    |    |    |    |    |    |     |
|----------------------------------------|----|----|----|----|----|----|-----|
| Staff baseline interviews              | 5  | 5  | 5  | 5  | 5  | 5  | 30  |
| Staff post implementation interviews   | 5  | 5  | 5  | 5  | 5  | 5  | 30  |
| Patient post-implementation interviews | 10 | 10 | 10 | 10 | 10 | 10 | 60  |
| TOTAL                           | 20 | 20 | 20 | 20 | 20 | 20 | 120 |

\* Distribution of staff interviews at baseline and post-implementation may vary depending on participants' availability and staffing levels at each site, but will be approximately 5 in each case.

## 2.2. Demographic characteristics

The cases identified through administrative data consists of individuals with OUD who are hospitalized at one of the six study sites. We anticipate that the characteristics of this population will vary by site, given the differences in patient populations served by each of the participating hospitals. Overall, we expect that cases will have the following demographic characteristics: 28% female; 14% Hispanic; 24% Black, 37% White, 1% Asian, 38% mixed race/other; 4% age 18-25, 33% age 26-45, 55% age 46-65, 7% >65 years.

Characteristics of individuals who are enrolled in the study and participate in interviews will reflect the groups from which they are drawn, and are not expected to vary substantially according to study site. Our purposive sampling approach will seek to enroll participants with a range of demographic characteristics. No one will be excluded from participation on the basis of gender, race, or ethnicity. The expected demographic characteristics of participants are indicated below in Table 4, though the actual demographic characteristics of enrolled individuals may differ.

**Table 4. Expected demographic characteristics of the population enrolled for participation in interviews**

| Groups | Staff-Medical providers | Staff-Counselors | Staff-Peers | Patients |
|---------------|--------------------------------|-------------------------|--------------------|-----------------|
|               | N                       | N                | N           | N        |
| TOTAL         | 20                             | 20                      | 20                 | 60              |
| Sex           |                                |                         |                    |                 |
| Female        | 12                             | 12                      | 10                 | 17              |
| Ethnicity     |                                |                         |                    |                 |
| Hispanic      | 2                              | 8                       | 2                  | 8               |
| Race          |                                |                         |                    |                 |
| Black         | 4                              | 8                       | 7                  | 14              |
| White         | 14                             | 8                       | 7                  | 22              |
| Asian         | 2                              | 0                       | 0                  | 1               |
| Multi/Other   | 0                              | 4                       | 6                  | 23              |
| Age group     |                                |                         |                    |                 |
| 18-25         | 0                              | 0                       | 3                  | 3               |
| 26-45         | 10                             | 10                      | 7                  | 20              |
| 46-65         | 10                             | 10                      | 7                  | 33              |
| >65           | 0                              | 0                       | 3                  | 4               |

## 2.3. Inclusion and exclusion criteria

Case definition for inclusion in the analysis of administrative data:

1. Adult patients ( $\geq 18$  years);
2. Hospitalized for at least 1 night on an inpatient service (not including intensive care or prison units);

Effectiveness of the Consult for Addiction Treatment and Care in Hospitals (CATCH) model for engaging patients in opioid use disorder treatment: Pragmatic trial in a large municipal hospital system  
9.7.2023

3. Admission or discharge diagnosis (based on ICD-10 codes) of opioid use disorder or opioid poisoning. Cases are excluded if they received MAT (buprenorphine, methadone maintenance treatment, or naltrexone) in the 30 days prior to admission. Cases included in the intervention condition must have been admitted on a date following implementation of CATCH.

Inclusion and exclusion criteria for interview participants:

Inclusion criteria:

- Age 18 years or older
- Hospitalized with ICD-10 admission or discharge diagnosis of opioid use disorder or opioid poisoning.

Exclusion criteria:

- Lack of fluency in English, unable to provide informed consent.

Based on these inclusion and exclusion criteria, cases admitted to hospital units that are not served by the CATCH program (i.e. inpatient psychiatry, detoxification unit) may appear in the analytic dataset. Some of our analyses will exclude cases from these units.

Inclusion criteria for exploratory analyses:

1. Adult patients ( $\geq 18$  years);
2. Hospitalized for at least 1 night on an inpatient service (not including intensive care);
3. Alcohol use disorder, alcohol poisoning, other substance use disorder, adverse effects of substance use, illicit drug poisoning.

Exclusion criteria for exploratory analyses:

None

**2.4. Vulnerable subjects**

We do not exclude pregnant women from participation in this minimal risk study. No other vulnerable populations are enrolled.

**3. Methods and procedures**

**3.1. Sources of materials**

Administrative data

The administrative data sources are listed below, and the measures to be extracted from each data source are listed in Appendix A.

- *Medicaid claims* are the primary data source. The Medicaid claims dataset contains information on all health care contacts and paid claims, including inpatient hospitalization, emergency department visits, outpatient visits to medical or addiction treatment providers, and filled prescriptions for medication. New York University has an existing data exchange application and agreement (DEAA) with the NYS Dept. of Health that covers the use of NYS Medicaid claims data, including personal health information and Medicaid Confidential Data. The scope of the proposed research falls under this existing agreement.
- *H+H clinical data warehouse* is a supplemental data source. The clinical data warehouse contains electronic health record (EHR) data from all H+H facilities. This data may include insurance and demographic information, provider notes, diagnoses, problem list, test results (laboratory, radiology, etc.), medication orders and prescriptions, filled prescriptions from H+H pharmacies, and location of the admission. Through the NYU-H+H Clinical and Translational Science Institute, Master Data Use Agreements have been created between H+H and NYU Grossman School of Medicine. The Master Data Use Agreements govern the sharing of data for research and specify the type of data that may be shared. In addition to the Master Data Use Agreements, NYU investigators will complete data request forms that specify the data elements to be transferred.
- NYC Dept. of Health and Mental Hygiene (DOHMH) *comprehensive database of NYC overdose deaths* is a

supplemental data source. The DOHMH Bureau on Alcohol and Drug Use compiles a database that links the NYC Vital Statistics Death Registry (death certificates recording cause of death), to NYC Medical Examiner Data files that document overdose deaths and all substances involved in the death. This dataset is developed and maintained by the NYC DOHMH, and the full identified data set cannot be shared with outside investigators. The extraction of measures for this study will be performed by a DOHMH data analyst who works with Vital Statistics and Medical Examiner data files.

- *CATCH program data* are collected for measurement of intervention fidelity. It will be collected by the research team on a monthly basis, or less frequently depending on the availability of the information, for a total of 12-41 months after CATCH introduction at each site. These data includes information on staffing, preparations for the delivery of services, intervention adherence, telephonic outreach and supervision. CATCH program data will also be analyzed to measure the impact of the COVID-19 pandemic on CATCH Program activities.
- A structured review of medical records for approximately 100 patients at each study site will be conducted by the research staff. This review will assess the rate of under-coding of OUD in billing data and medical records. The review will include patients who received MAT in the hospital to determine whether these patients should have a diagnosis of OUD. Research staff will compare the chart review findings to the ICD-10 diagnostic codes used for the hospitalization to determine the frequency with which OUD is not captured in diagnostic coding. If fewer than 90% of patients identified in the chart review have an ICD-10 discharge diagnosis of OUD or poisoning, the research team will revise their process for identifying cases eligible for CATCH services.
- As part of the data quality checking process for our analytic dataset, the research team may conduct additional chart reviews to confirm details about variables outlined in the protocol. For example, we will seek to determine or confirm the eligibility of the admission location (i.e., to exclude admissions to inpatient psychiatry, detoxification units, prison units). We plan to use the H+H Epic EHR to look up hospital admissions that meet our case definition. Trained research assistant(s) will search for cases in the EHR using one or more individual identifiers from the H+H clinical data warehouse and/or Medicaid data sets. Once the case is identified in the EHR, information will be entered directly into the secure data environment hosted in the MCIT Data Center or onto the encrypted external hard drive that is used to store Medicaid data (See Section 3.5). Note that this process does not aim to identify additional patients who meet our case definition; rather, we will be collecting additional data from the charts of the patients we already identified.
- Data for the AUD exploratory measures will be directly accessed through the Epic EHR for Bellevue Hospital. The patients will be selected from a database of all patients who have a completed CATCH consult at Bellevue between 07/01/2019 – 02/29/2020 inclusive who meet our inclusion/exclusion criteria for this exploratory analysis. We will then collect data items noted in the “CATCH Exploratory Alcohol Use Disorder Chart Review Form”. Information will be directly entered into a secure NYU Langone Health (NYULH) REDCap (Research Electronic Data Capture) database. After data collection is complete, all individual identifiers will be removed from the analytic dataset, and individuals will be identified by study-assigned unique identifiers.
- Only members of the research team will have access to the study data. All research data for the AUD exploratory analyses will be extracted from the parent administrative dataset and securely transferred to a REDCap database that is provided and hosted by NYU Grossman SoM Research IT. REDCap is a HIPAA compliant secure web application for building and managing databases. REDCap provides audit trails for tracking data manipulation and user activity, and automated export procedures for data downloads to statistical programs. The NYULH REDCap database will be built and maintained by study staff, with support from NYU Grossman SoM Research IT. The database will be a HIPAA compliant, locally managed storage cluster on a secure, password-protected share drive accessible only to members of the research team. Passwords will be changed on a regular basis.

### Qualitative data

Interviews will be conducted with CATCH staff and patients using IRB-approved interview guides that are based on the CFIR framework. [name] has substantial experience conducting qualitative interviews with medical staff and patients.

## **3.2. Procedures for data collection**

### Administrative data

9.7.2023

Before extracting the administrative data, the investigators and data analysts will jointly develop criteria for defining each measure in the EHR. They will develop a comprehensive data dictionary, and establish a procedure for extracting these data for analysis. Measures from each data source will be extracted and cleaned by a designated data analyst who has prior experience conducting similar projects in their specified data set. Analysts will work under the supervision of the key personnel who have specific expertise utilizing the data source ([name] for Medicaid claims, [name] for the H+H clinical data warehouse, [name], [name] and [name], for the DOHMH overdose data). In the final data set used for analysis, individuals will be identified by unique ID numbers, and any personal identifiers will be removed.

For the Medicaid claims and H+H clinical data warehouse data, the data analysts will provide a data set to the NYULH biostatisticians that includes personal identifiers that enable matching across the data sets, along with the variables specified in the study's data dictionary. To generate the overdose data set used in our planned analyses, the NYULH data analyst will identify individuals within the Medicaid and/or H+H datasets who had no activity after month 12 following hospital discharge, and provide a limited set of identifiers (which may include any of the following: name, date of birth, sex, last 4 digits SSN), derived from the H+H data set, to the DOHMH overdose data analyst. The DOHMH data analyst will use these identifiers to identify any matches in the DOHMH overdose data. After data matching is completed, and before the data are transferred to NYULH, all individual personal identifiers will be removed other than a study ID. CATCH program data will either be entered by NYULH research staff or it will be entered by CATCH staff and program administrators into an electronic form provided by the research team.

All data containing PHI will be transferred through a secure file transfer platform. Data management will be the responsibility of the biostatistics team, who will verify the integrity and completeness of the data received, and will perform additional cleaning as needed, prior to analysis. Quality of the data extracted from each administrative data set will be evaluated and monitored by the data analysts and co-investigators working with each data source. Primary responsibility for quality assurance of data extracted from each of these sources lies with [name] for the Medicaid claims data, [name] for the H+H clinical data warehouse data, [name] and [name], [name] for the DOHMH database of OD deaths.

After data are received from each data source by the biostatisticians at NYU Grossman SoM, ongoing evaluation and monitoring of its quality will be part of data management activities. They will review the data received to ensure its completeness and accuracy. They will also review the data checking or validation reports to determine the number and types of data issues and look for trends in data collection patterns within and across sites. The biostatisticians will specifically look for invalid data, missing data, data in conflict with the specifications of the study, and data in conflict with the within- and across-record logic checks. They will also review the data longitudinally for consistency and will look for outliers or data that may exceed actual and logical limitations of each data element (i.e., range checks). They will communicate all data issues and trends to the PI and other members of the study team and work with them to rectify all issues to maintain the highest possible level of data completeness and accuracy.

#### Qualitative data

Interviews will be audio recorded. Audio recordings of interviews will be sent to professional transcription services and transcribed verbatim. Names and other identifying information will be removed from the transcriptions.

### **3.3. Data analysis**

#### 3.3.a. Administrative data analysis

Analysis of the administrative data is led by the Senior Biostatistician, who will direct the analysis in collaboration with the PI, and will direct and supervise the work of one or more biostatistician(s) in carrying out the statistical programming and data management. No interim analyses are planned. The Statistical Analysis Plan attached to this protocol contains detailed information on the analysis.

Sensitivity analysis: Because substance use diagnoses are not always completely captured in diagnostic coding, we will also perform a sensitivity analysis on a subset of approximately 100 patients from each facility who received once daily methadone or any formulation of buprenorphine-naloxone while hospitalized during the TAU period, as determined from EHR data collected in the H+H clinical data warehouse. A structured chart review will determine whether these

patients have OUD. If fewer than 90% of patients identified in the chart review have an ICD-10 discharge diagnosis of OUD or poisoning, we will revise our process for identifying cases in the administrative data.

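### The 90% coding check samples only usual-care patients given MAT in hospital and ignores the 30-day MAT exclusion, so it cannot show a coding change under CATCH and may not represent the analysed cases

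*Protocol*

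**What the plan says.** Section 2.3 of the protocol admits a case to the analysis on an "Admission or discharge diagnosis (based on ICD-10 codes) of opioid use disorder or opioid poisoning". It then removes recent treatment: "Cases are excluded if they received MAT (buprenorphine, methadone maintenance treatment, or naltrexone) in the 30 days prior to admission".

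Because coding may be incomplete, Section 3.3.a plans a structured chart review in "a subset of approximately 100 patients from each facility", namely those "who received once daily methadone or any formulation of buprenorphine-naloxone while hospitalized during the TAU period". The decision rule is: "If fewer than 90% of patients identified in the chart review have an ICD-10 discharge diagnosis of OUD or poisoning", then "we will revise our process for identifying cases in the administrative data".

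Section 3.1 describes what appears to be the same review, with about 100 patients per site and the same 90% threshold. It names no period. On the sample it says: "The review will include patients who received MAT in the hospital to determine whether these patients should have a diagnosis of OUD". Below 90%, it says that "the research team will revise their process for identifying cases eligible for CATCH services".

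Section 1.1 states that CATCH teams themselves assess inpatients to diagnose OUD and start MAT.

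**The concern.** Who enters the analysis depends on whether OUD was coded, and the intervention includes a team whose job is to diagnose OUD. If coding becomes more complete after go-live, the CATCH-period cases include patients of a kind that would have been missed under TAU. The two periods then differ in case mix as well as in care. A check drawn from TAU alone says nothing about coding under CATCH.

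The sampled group also differs from the analysed group in two ways. Patients who were already on MAT before admission and were continued on it in hospital can be sampled, yet Section 2.3 excludes them from the analysis. Patients with OUD who received no MAT in hospital, where under-coding may be greatest, are outside the Section 3.3.a sample.

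At stake are the comparability of the primary denominators and the soundness of any change to the case definition that the rule sets off.

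**Working it through.** **The plan's own figure.** The 90% is a chosen threshold with no derivation, so there is nothing to reproduce.

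**Step 1: what the check can estimate.** Let s0 and s1 be the share of true OUD cases that are coded in the TAU and CATCH periods. A TAU-only sample gives information on s0 and none on s1, so s1 − s0 cannot be estimated. This needs no assumed figures. No other part of the protocol fills the gap. The longitudinal data review in Section 3.2 concerns consistency of extracted data, not codes against chart-confirmed OUD. The additional chart reviews in Section 3.1 collect more detail on cases already found and do not look for missed ones.

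**Step 2: possible effect on the primary comparison.** From Section 1.8: TAU initiation 7%, and 4,500 cases per period. Assumed: s0, s1 and the initiation rate r of newly coded patients. With no true effect,

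CATCH rate = (s0 × 7% + (s1 − s0) × r) / s1.

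For s0 = 80%, s1 = 90%, r = 30%: (0.80 × 0.07 + 0.10 × 0.30) / 0.90 = 0.086 / 0.90 = 9.6%.

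| Coding, TAU to CATCH | r = 2% | r = 7% | r = 15% | r = 30% |
|---|---|---|---|---|
| 90% to 95% | 6.7% | 7.0% | 7.4% | 8.2% |
| 80% to 90% | 6.4% | 7.0% | 7.9% | 9.6% |
| 70% to 90% | 5.9% | 7.0% | 8.8% | 12.1% |

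The shift runs from about −1 to +5 points and is zero when r equals the TAU rate. For 80% to 90%, a two-sided 0.05 test of two proportions with 4,500 per period would reject in 18%, 36% or 99% of trials at r = 2%, 15% or 30%. That calculation ignores clustering, so it is only indicative.

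In the first row TAU coding sits at the threshold. At a true 90%, the chance of an observed share below 90% is 0.42 with 100 charts and 0.47 with 600 (exact binomial), so the rule need not flag that shift.

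**Step 3: does the sample represent eligible patients?** Let f be the share of the sample with MAT in the 30 days before admission. The protocol does not give f. Assume coding of 95% in that group and 70% in eligible patients. The check then shows f × 95% + (1 − f) × 70%.

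| f (assumed) | Coding shown | Chance the rule triggers, 600 charts pooled | Eligible charts per site |
|---|---|---|---|
| 50% | 82.5% | 1.00 | 50 |
| 75% | 88.8% | 0.82 | 25 |
| 90% | 92.5% | 0.01 | 10 |

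Poor coding in eligible patients is hidden only when f is high.

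**Step 4: the two descriptions side by side.** Section 3.3.a fixes the TAU period; Section 3.1 states none. Section 3.3.a revises how cases are found in the administrative data; Section 3.1 revises how cases eligible for CATCH services are identified. The rule counts discharge diagnoses only, while Section 2.3 accepts admission or discharge diagnoses.

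**The case against.** The check was designed to measure under-coding, not a difference in coding between periods, and the statistical analysis plan, which was not available here, may add a CATCH-period sample. Section 3.1 states no period, and its wording on whom the review includes is not exclusive. Its reference to cases eligible for CATCH services may simply be loose wording for analytic cases. The possible bias is also small beside the 15 to 25 point increase that Section 1.8 aims to detect.

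Much of this stands. The TAU restriction rests on Section 3.3.a alone, and the difference over what is revised may be one of wording. Both are reasons to reconcile the two sections. None of it gives the check, as Section 3.3.a describes it, any information on coding under CATCH.

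A reader might go further and infer that the sample is mostly ineligible, or that the rule will pass while eligible patients are badly under-coded. The protocol supports neither. It gives no share already on MAT, and Step 3 shows that the rule would still usually trigger at a share of 50% or 75% under the assumed coding rates. Nor do the documents show that the primary result is biased in favour of CATCH: the sign depends on how often newly coded patients initiate, which is unknown.

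**Conclusion.** The point holds in a limited form. Followed as written in Section 3.3.a, the check cannot show whether coding of OUD changes when CATCH starts. It also includes an unknown, possibly large, share of patients whom Section 2.3 would exclude. The first statement is logical and rests on no assumed figure; the second follows from the absence of the exclusion in both descriptions of the check.

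The size and direction of any bias are not established. Under the assumed coding changes the initiation rate moves by about −1 to +5 points with no true effect, and not at all if newly coded patients initiate at 7%. That would not by itself produce an effect of the targeted size, but it could distort the estimate. The check should be changed; the finding does not undermine the trial's design.

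**What to change.** - Keep about 100 charts per site, but draw them from both the TAU and the CATCH period.
- Apply the 30-day prior-MAT exclusion before sampling, or report eligible patients separately.
- Count admission or discharge codes, as the case definition does.
- Compare coding sensitivity between periods.
- State that any revised case definition applies identically to both periods and does not use in-hospital MAT as a criterion, because CATCH is designed to increase it.
- Reconcile Sections 3.1 and 3.3.a on the period sampled and on what is revised below 90%.

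The chart count does not rise, but there are two costs. The TAU estimate becomes less precise: at 90% coding, the 95% half-width per site is 1.96 × √(0.09/100) = 5.9 points with 100 charts and 1.96 × √(0.09/50) = 8.3 points with 50. With an even split pooled over six sites (300 charts per period, clustering ignored), the half-width for the difference between periods is 1.96 × √(2 × 0.09/300) = 4.8 points. Prior MAT must also be linked before charts are drawn.
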